## Abstract

Background: Stress is a significant public health concern that can be self-evaluated using the job control demands model from Karasek. Emergency health care workers are particularly exposed to stress because of the intrinsic characteristics associated with the job (i.e., life-threatening emergencies, overcrowding, lack of bed spaces). However, these attributes have never been studied using the Karasek model. Methods: An observational, prospective, multicentric study in French Emergency Departments will be conducted using a cohort of emergency health care workers. Four questionnaires before a control day and after a nightshift will be assessed every 5 years in the same emergency departments. Also, the Karasek questionnaire, a sociodemographic questionnaire, the Maslach Burnout Inventory scale, the Hospital Anxiety, Depression Scale, and a food intake questionnaire will be evaluated. Salivary biomarkers (cortisol, immunoglobulin A, lysozyme) will be collected from every emergency health care worker who consents to participating in the study. Conclusion: This study will provide a point of care for the emergency health care workers’ stress situation every 5 years. Ethics: This protocol was registered in Clinical Trials under the identification NCT02401607 after the French Ethics Committee’s approval.

## 1. Background

Chronic stress at work is a significant public health problem increasing morbidity and mortality [1]. Many employees complain about “stress” at work. In the medical field, burnout prevalence near or exceeding 50% has been documented in national studies conducted in both physicians in training and practicing physicians [2]. This is especially true in the Emergency Departments. Emergency health care workers are a particularly at-risk population. Indeed, their work is a complex interaction between stress due to life-threatening emergencies; overcrowding of the Emergency Department; lack of sleep; bad food repartition before, during, and after shifts; and accumulated fatigue [3]. Health care workers are considered as high-risk group for death by suicide [4]. Although men a higher risk of suicide in the general population, female physicians have higher suicide rates than men [5]. Specialties with a heavy workload, long shifts, and unpredictable hours (associated with sleep deprivation); stress-related situations (life and death emergencies) [6]; and easy access to a means of committing suicide [7] are particularly at risk of suicide [4,8,9]. Emergency health care workers are shift workers with scheduling irregularities regarding hours, duration, and holidays. Shift workers have bad well-being [10] and cardiometabolic risk factors (higher blood pressure [11], higher levels of triglycerides [12], higher risk of obesity [13], higher risk of heart disease [14], and higher metabolic syndrome [15]). Even if quantitative energy intake is the same between nightshift workers and day workers [16], qualitative food choices and habits are different [16]. Shift workers consume more snacks, alcohol, and confectioneries and eat more frequently during the night [17], which possibly hurts circadian regulation [18]. This dysregulation is mainly impacted by the inappropriate secretion of insulin, ghrelin, and leptin [19], leading to diabetes [20]. To our knowledge, no study has evaluated the food intake of emergency physicians before nightshift, during nightshift, and after nightshift.

One way of measuring stress at work is the use of a self-reported psychological questionnaire. Among them, the job control demand model from Karasek is widely used to evaluate psychosocial factors at work [21,22]. It defines job demands and job control as the two broad work-related characteristics present in the environment of most occupations that can be incredibly stressful. Job demands refer to the psychological needs imposed by daily working activities such as mental workload, organizational constraints, and various types of conflicts (i.e., of the role, demands). Job control refers to the lack of decision latitude, specifically the freedom workers can have in realizing their job. Job control is composed of two components: Skill discretion (possibilities to use one’s skills) and decision authority (chances of making decisions that can reduce adverse effects of high psychological demands). Workers can perceive both job demand and job control as being low or high. The combination of high job demands and low job control results is called ‘job strain.’ This situation is the most aversive possible combination. Workers in the ‘job strain’ configuration are particularly at risk of low well-being [23], burnout [24], and ill-health [25], such as cardiovascular diseases [26,27].

Moreover, the Karasek job strain model is an independent predictor of acute coronary events [28]. Conversely, a combination of low demand and high control results in ‘low strain.’ The authors proposed an extension of the model in the 1980s to include another dimension: Worksite social support [29]. Support from colleagues and/or from the hierarchy acts as a buffer against complex combinations of job control and demands.

The Karasek job strain model has been assessed in 25,000 workers in the French SUMER study and classified as the main types of occupations [30]. However, no data regarding emergency health care workers’ scores at the Karasek questionnaire are available, even though burnout exposure is a well-known problem among health care workers [31,32]. This absence is regrettable as emergency health care workers often need to deal with life-threatening emergencies in a short amount of time, regularly following long shifts [33]. Karasek’s questionnaire is supposed to assess a long-term stable perception of work, despite the absence of a study comparing Karasek scores within different conditions in the same participant. It is also essential to explore protective factors that might help alleviate perceived stress and are relatively easy to integrate into medical organizations or daily lifestyle [34].

Regarding biological indicators of stress, several biomarkers of stress have been proposed [33,35,36]. To our knowledge, the relationships between biomarkers of stress and the Karasek job strain model have never been investigated. 

We are also interested in finding a precise way to evaluate work stress. Studies have shown contradictory results on biological markers of stress. The present study will use multiple stress markers, allowing for improved and more comprehensive results pertaining to how psychological stress interacts with biological variables.

Cortisol is the historical marker of stress. Nevertheless, several studies have not found modifications in cortisol levels. Thus, no correlations have been demonstrated between secretions of salivary cortisol and stress questionnaires among neonatal health care professionals [37]. Other studies have reported some underlying effects. For example, teaching, a profession with high levels of job stress and burnout, is associated with a significantly higher level of salivary cortisol during workdays versus free days [38].

Among the different biomarkers, our team previously highlighted the potential of salivary dehydroepiandrosterone (DHEA) to assess stress due to its stability (steroid) and its long half-life of 16 h [39]. Related to cortisol, some results have suggested that salivary DHEA levels are modified under stress [40]. Levels of salivary DHEA are also increased in anxiety symptoms [41]. The salivary DHEA’s half-life is about 15 h, making it a relatively stable concentration throughout the day, unlike cortisol. Therefore, salivary DHEA is an interesting marker.

Few studies have examined the response of salivary IgA in the case of work-related stress [42]. A recent study described the opposite relationship between stress and salivary IgA levels among healthy volunteers after a psychological stressor [43]. This marker’s advantages are its ease of access (saliva) and relatively long half-life (10–15 days), which makes it relatively stable.

Salivary lysozyme has been rarely studied. It does not appear to be modified after acute physical stress on healthy men [44], but studies have found but a negative correlation in university students during their final license exam [45] and in 50 male workers on an assembly line in China [46].

Most biological parameters mentioned here are related to personality questionnaires (locus of control, self-esteem) or perceived health (depression, quality of life, psychosomatic complaints). This will allow us to correlate participants’ perceptions of biological modification.

We performed a pilot study with 19 emergency physicians at the Clermont-Ferrand University Hospital. The Karasek questionnaire interview results showed a low decision latitude (59.67 ± 6.44; score below 71) and a high psychological demand (29.39 ± 4.07; score below 20) in this population, illustrating the definition of a stressful work situation (high workload with low autonomy). This state was fortunately balanced by a critical perceived social support (29.94 ± 3.21; score greater than 24). The results demonstrate a perfect illustration of inadequacy between professional demands (taking care of patients regardless of their numbers, varying according to hours and days) and organizational constraints (lack of beds spaces, for example, a situation where decision latitude is nonexistent, generating stress). Our pilot study permits us to situate the emergency physicians on the SUMER study, which lists the mean scores of psychological demands and decision latitude by professional family. This comparison highlights emergency physicians’ extraordinary situation, with decision latitude among the lowest and the highest psychological needs. Thus, it becomes interesting to appraise stress in this population through seeking solutions to reduce burnout.

Therefore, the objective of this manuscript was to present the design of a study protocol to examine well-being in emergency health care workers (the SEEK-study). The acronym SEEK is “Study on Emergency physicians’ responses Evaluated by Karasek questionnaire”. The primary objective is to assess and determine Karasek scores in a large sample size of emergency health care workers. The secondary objectives is to evaluate whether there is a change in work perception both in the short term (on leave and after a nightshift) and long term (with the reproducibility of this study every 5 years). Secondly, we will evaluate the food intake before, during, and after the nightshift and explore its relationship with Karasek’s score and stress biomarkers. We will further explore Karasek’s associations with some biomarkers of stress and protective factors.

## 2. Materials and Methods

### 2.1. Study Design

Our study will be an observational and prospective study. It will be a multicenter, French study based on the observation of healthy volunteers without invasive sampling in France. We will record different variables and data from the study population without interventions. The study design is described in Figure 1. We will provide repeated measures in the same departments (each measurement time comprising of 24 h, including a nightshift, and 24 h, including a dayshift). We will create a cohort of workers that will be followed every 5 years if they are still working in the Emergency Department. However, we can include new health care workers if needed.

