### 2.2. Study Settings

According to our pilot study, we evaluate the time required by the participant at about 15 min per phase.

For the first phase, investigators will assess the Karasek’s questionnaire, food intake questionnaire, Maslach Burnout Inventory, and Hospital Anxiety Depression Scale (HAD) among Emergency health care workers at the beginning of the control day (around 8:30 am). A sample of saliva in an Eppendorf will be recovered at the same time. Saliva collection will be brought in a cooler to the Institute of Occupational Medicine of Clermont-Ferrand by the end of the day. The samples will be stored at −80 °C. The experimenter will also deliver a pre-stamped envelope for the return of 2 Eppendorf tubes (saliva collection) and questionnaires at the end of the day.

Considering the difficulties of obtaining homogenous planning with all emergency providers, the time passed between the first and the second phase will not be the same between all providers. However, the 2 phases need to be separated by at least 1 week.

For the second phase, investigators will assess the same questionnaires with the saliva collection at the beginning and the end of a 24-hour or 14-hour nightwork session (up to 1 week later). This will permit the evaluation of the relationships between modifications in questionnaire answers and biological responses by comparing results during a control day versus results at the end of a work session, including a nightshift.

The third phase of the SEEK protocol is a longitudinal follow-up. This study design will be reproduced every 5 years in all Emergency Departments. If possible, i.e., if they are already in the same Emergency Department, we will follow-up on the initial cohort. We choose a follow-up of 5 years because it corresponds to the residency program duration in Emergency Medicine in France. We will program 4 sessions for a total of 20 years.

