### 2.5. Recruitment Process

During each part of the study, 120 emergency health care workers will be recruited as participants. During the recruitment phase, all emergency health care workers will individually receive an information letter attached by email. Acceptance or refusal will be given by mail to avoid any subordination effect between the experimenter and the recruited. If they agree, they will have 8 days to sign the consent form to participate in the study. For privacy purposes, the question about their medical history will not be asked by email. Instead, a list of non-inclusion criteria will be given in the information letter. Thus, if any exclusion criteria are present, they can refuse participation without any need for further explanation.

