### 3.3. Data Analysis

Continuous variables will be presented as mean and standard-deviation or median and interquartile range according to the statistical distribution. The normality assumption will be assessed using Shapiro–Wilk test. Categorical variables will be expressed as numbers and associate percentage. The primary analysis will be mainly descriptive and will define the perception scores of emergency physicians work according to the Karasek questionnaire for each dimension composing the score (decision latitude, psychological demands, and social support), as quantitative and categorical variable. A correlation matrix analysis on quantitative variables (i.e., Karasek questionnaire and other psychological questionnaires) will be conducted using Pearson or Spearman correlation coefficients, in addition to principal component analysis (PCA). The Karasek questionnaire score’s evolution, obtained for each dimension, will be tested with a paired two-sample Student’s test, or nonparametric Wilcoxon test if necessary. Linear regression models and random-effects models will complete these analyses. These models will permit, with multivariable analyses and covariates’ introduction, to seek possible explanatory factors of the Karasek score (a dayshift (control) versus the end of 24 h or shift) and its evolution. The same statistical analysis plan will be used for continuous parameters collected after the dayshift (control) and after the 24-h shift (e.g., all biological samples). For categorical variables, Stuart-Maxwell test will be used. The comparisons for quantitative parameters (e.g., biological data, questionnaires’ scores) will be based on Student’s *t*-test or nonparametric Mann–Whitney test. The comparisons involving categorical parameters (gender, seniority) will be made with the Chi-squared test or Fisher’s exact test. All statistical analyses will be performed as two-sided tests, with a *p* < 0.05 considered as significant. Statistical analyses will be performed using the Stata software (version 16, StataCorp, College Station, TX, USA).

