## 5. Conclusions

This project will contribute to an overview of emergency health care workers’ conditions. The omission of their place in the SUMER study after the Karasek questionnaire will be corrected. Second, the outcome from this study, repeated every 5 years over 20 years, will provide an insight into whether or not improvements have occurred in the emergency health care working conditions and, if so, how this outcome will influence or impact health care policy. Last, the secondary outcomes will probably give our team the impetus to improve life quality by increasing quality and quantity of food intake or by the impact of new Emergency Department organization between two measures.

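### Following only workers who stay, with newcomers added as needed, cannot by itself show that working conditions changed over 5 years

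*Protocol article*

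**What the plan says.** The objectives at the end of section 1 include change in work perception in the "long term (with the reproducibility of this study every 5 years)". Section 2.1 defines who is followed: "We will create a cohort of workers that will be followed every 5 years if they are still working in the Emergency Department". It adds: "However, we can include new health care workers if needed". Section 2.2 narrows this to the same department: "If possible, i.e., if they are already in the same Emergency Department, we will follow-up on the initial cohort". It plans four sessions over 20 years and justifies the 5-year interval because "it corresponds to the residency program duration in Emergency Medicine in France". Section 2.5 gives the recruitment target: "During each part of the study, 120 emergency health care workers will be recruited as participants".

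The results are then given a causal reading. The Discussion says that 20 years of follow-up will allow the impact of local and national policy on workers' well-being to be assessed. The Conclusions say that the repeated study "will provide an insight into whether or not improvements have occurred in the emergency health care working conditions". Potential Limitations names self-report and the uncontrolled demands of individual work sessions. It does not mention leaving, turnover or composition.

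**The concern.** A worker contributes to a later session only by remaining in the same department. Section 1 itself links job strain to low well-being, burnout and ill-health, so it is plausible that leaving is related to the scores being measured. The place of those who leave may be taken by newcomers who differ in position and seniority.

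The article does not settle whether the 5-year contrast is change within the same workers or change in the department's workforce. These are different quantities. The first describes people who stayed. The second combines any change in conditions with a change in who is there. Neither, read alone, says whether conditions improved.

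The interval adds to this. Residents measured at one session will generally have finished residency by the next, so they will have left or changed position. The article does not give the share of residents or where they go afterwards, so this part is inference.

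At stake is the reading of a secondary objective that carries the article's policy claim. The primary analysis is descriptive and is not affected.

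**Working it through.** **Inputs.** The pilot SDs in section 3.1 are 6.44 (decision latitude), 4.07 (psychological demand) and 3.21 (social support), with a within-person correlation of 0.5. The article gives no turnover and no difference between leavers and stayers. I assume turnover p = 0.3 to 0.6 and leavers worse than stayers by d = 0.3 to 0.8 SD. True change is set to zero throughout.

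**The plan's own figures.** Section 3.1 states detectable differences of 2.35, 1.48 and 1.17 for 100 subjects, 5% two-sided and 95% power. With correlation 0.5 the SD of a difference is SD × √(2 × 0.5) = SD.
- Normal approximation: 6.44 × (1.960 + 1.645)/√100 = 2.32, and likewise 1.47 and 1.16.
- Noncentral t: 2.34, 1.48 and 1.17.

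The figures reproduce. They are stated for control day versus end of nightshift, so they say nothing about the 5-year contrast. In SD units they are about 0.36 (2.35/6.44 = 0.365), which I use below for scale only.

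**Shift in the session mean.** Set the original cohort mean at 0. Stayers then lie at +p·d in the favourable direction.
- Entrants resemble the original cohort: shift = (1 − p) × p·d + p × 0 = p(1 − p)d. Lowest: 0.3 × 0.7 × 0.3 = 0.063 SD. Highest, at p = 0.5: 0.5 × 0.5 × 0.8 = 0.20 SD.
- Entrants resemble stayers: shift = p·d. Lowest: 0.3 × 0.3 = 0.09 SD. Highest: 0.6 × 0.8 = 0.48 SD.

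| Dimension | SD | Entrants like original cohort | Entrants like stayers |
|---|---|---|---|
| Decision latitude | 6.44 | 0.41 to 1.29 | 0.58 to 3.09 |
| Psychological demand | 4.07 | 0.26 to 0.81 | 0.37 to 1.95 |
| Social support | 3.21 | 0.20 to 0.64 | 0.29 to 1.54 |

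The table gives points on each scale, all in the favourable direction (for demand, a fall). If entrants resemble the original cohort, the shift stays below 0.36 SD. If they resemble stayers, the range crosses it.

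**Within-worker change in stayers.** I simulated baseline score, follow-up score and propensity to stay as jointly normal, for decision latitude, with 100 workers at baseline and 4,000 runs per scenario. Assumed retention was 80%, 60% or 40%, and the correlation of the score with staying was 0.2, 0.3 or 0.5.
- Leaving depends on the later score: mean change in stayers is +0.23 to +1.56 points, and a nominal 5% test rejects in 6% to 34% of runs.
- Leaving depends on the baseline score: mean change in stayers is −0.22 to −1.55 points, with rejection in 7% to 32%.

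The closed form agrees. The apparent change is ±(1 − 0.5) × correlation × SD × φ(z)/retention, where z is the normal quantile of the retention. At 40% retention and correlation 0.5 this is 0.5 × 3.11 = 1.56. The sign depends on why people leave, which the article does not plan to find out.

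**The case against.** The strongest counter-argument is that section 3.3 already plans linear and random-effects models with covariates, and that sections 3.2.4 to 3.2.6 collect sex, workplace, position and seniority. An article may leave the model structure and missing-data handling to a fuller plan. That stands, and missing model detail is not the point here. But a random-effects model with a single session effect blends change within stayers with the difference between newcomers and leavers. Nor does it protect against leaving that depends on scores never observed. The fault is the follow-up rule combined with the stated interpretation.

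The size can also be disputed. Turnover and the leaver difference are both assumed. If the first-session sample is itself the product of steady turnover, and that turnover continues unchanged, the session mean need not shift at all. This stands too, so no single figure can be defended.

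Three stronger readings are tempting but not supported.
- A reader might infer that 5-year change will be tested by a paired test, because section 3.3 says the score's "evolution, obtained for each dimension, will be tested with a paired two-sample" test. That paragraph's named contrast is control day versus end of shift, and it does not say the paired test is the 5-year test. A paired test would also exclude newcomers, so they could not bias it.
- A reader might infer that all the precision and power in section 3.1 assumes 100 complete pairs over 5 years. The margins of error are one-sample figures. Only 2.35, 1.48 and 1.17 are paired, and they belong to the short-term contrast.
- A reader might infer that the bias must look like improvement. The simulation shows it can equally look like worsening.

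**Conclusion.** The concern holds in a limited form. Followed as written, the long-term objective cannot separate changed working conditions from selective leaving or changed workforce composition, yet the Discussion and Conclusions attribute the difference to conditions and policy without a caveat on turnover.

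The size is unknown. Under the assumed turnover and leaver differences, the session mean shifts by about 0.06 to 0.20 SD if entrants resemble the original cohort and by 0.09 to 0.48 SD if they resemble stayers. Steady turnover could bring it to zero. Change measured only in stayers can be biased in either direction. The sample-size figures in section 3.1 are not in question.

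**What to change.** For the 5-year contrast:
- Fit the random-effects model to all workers and all sessions, with session, position, seniority and sex as fixed effects and worker and department as random effects.
- Report two results separately: (a) within-worker change in stayers, and (b) change in department means standardised for position and seniority. In (a), use seniority at first measurement, because a stayer's seniority advances in step with the session.
- At each session, compare the previous Karasek and Maslach Burnout Inventory scores of leavers and stayers.
- Add a sensitivity analysis for non-random leaving.
- Limit the policy and improvement claims in sections 4 and 5 to what (a) and (b) support.

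The covariates and previous scores are already collected. The cost is extra analysis work, recording who has left at each session, and a more cautious conclusion. The article does not describe a record of leavers, so it should be kept from the first session; exits are hard to reconstruct years later.
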